### Objectives {7}

The primary aim of the iDoT-AFD study is to identify the molecular imaging biomarkers for AFD by analysis of KP metabonomics and multimodal magnetic resonance imaging (MRI). The secondary aim of the iDoT-AFD study is to find out the optimized intervention and the predictive biomarkers of treatment effectiveness in patients with AFD. The third aim of the iDoT-AFD study is to screen out the risk factors and build a clinical early warning model to predict the conversion of AFD to BD.

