### Eligibility criteria {10}

The inclusion criteria for patients with AFD are as follows: (1) 16–60 years old, (2) meeting the DSM-5 criteria for MDD, (3) scored 20 or higher on the Hamilton’s Depression Scale with 24 items (HAMD-24), (4) enough audiovisual ability and comprehensive ability to accomplish the interview, (5) necessary and appropriate to accept the treatment of antidepressants, (6) scored less than 14 on the Hypomania Symptom Checklist-32 (HCL-32), and (7) meeting DSM-5 specifier for atypical features: mood reactivity and 2 or more of the following—significant weight gain or increase in appetite, hypersomnia, leaden paralysis, and a long-standing pattern of interpersonal rejection sensitivity that results in significant social or occupational impairment.

The exclusion criteria for patients with AFD are as follows: (1) severe medical or neurological problems; (2) previous episodes of mania or hypomania; (3) female patients who are pregnant, planning to be pregnant, or breastfeeding; (4) high risk of suicide; (5) had ECT, MECT, or rTMS in the past 6 months; and (6) experienced severe personality disorder, mental retardation, and anorexia/bulimia nervosa.

Additionally, all included patients with AFD should be drug-naive or medication free for more than 1 week.

The inclusion criteria for patients with BD are as follows: (1) 16–60 years old, (2) meeting the DSM-5 criteria for major depressive episode of bipolar I disorder or bipolar II disorder, (3) scored 20 or higher on the HAMD-24, and (4) enough audiovisual ability and comprehensive ability to accomplish the interview.

The exclusion criteria for patients with BD are as follows: (1) severe medical or neurological problems; (2) female patients who are pregnant, planning to be pregnant, or breastfeeding; (3) high risk of suicide; (4) had electroconvulsive therapy, modified electroconvulsive therapy, or repetitive transcranial magnetic stimulation in the past 6 months; and (5) experienced severe personality disorder, mental retardation, and anorexia/bulimia nervosa.

The inclusion and exclusion criteria for HC are as follows: (1) 16–60 years old, (2) enough audiovisual ability and comprehensive ability to accomplish the interview, and (3) no history of mental disorder or serious somatic disease.

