##### Neuroimaging assessments

Neuroimaging data are acquired using the 3.0-T scanner at available clinical sites. Imaging data including structural MRI, rest state functional MRI, and diffusion tensor imaging (DTI)/diffusion kurtosis imaging (DKI) are collected. All participants are planned to be scanned at baseline, and patients with AFD will also be scanned at 12 weeks, 1 year, and 4 years.

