### Methods for additional analyses (e.g., subgroup analyses) {20b}

To explore the potential biomarker identifying AFD, analysis of variance (ANOVA), Kruskal–Wallis tests, or chi-square tests will be applied to compare the group differences of multivariate-dimension information among the first-episode AFD patients, recurrent AFD patients, and patients with BD and HC.

The prediction model of patients with AFD switching from depression to mania or hypomania will be constructed. Multidimensional data obtained at baseline and their changes during the follow-up period will be used to predict the binary outcome (switching to mania/hypomania or not). The concordance index will be calculated to assess the discrimination of the model. Construction of the multivariate prediction model will be conducted by collaborators specializing in biomedical engineering.

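### The AFD–BD biomarker comparison names only tests without covariates, although AFD patients must be off medication and BD patients need not be

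*Protocol article*

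**What the plan says.** Objectives {7} states: "The primary aim of the iDoT-AFD study is to identify the molecular imaging biomarkers for AFD", from kynurenine-pathway metabolites and multimodal MRI.

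Methods for additional analyses {20b} names the comparison that serves this aim. After ANOVA and Kruskal–Wallis tests, the sentence reads "chi-square tests will be applied to compare the group differences of multivariate-dimension information", and the groups are set "among the first-episode AFD patients, recurrent AFD patients, and patients with BD and HC". It names no covariate, site or medication term.

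Eligibility criteria {10} treats the two patient groups differently. For AFD, "all included patients with AFD should be drug-naive or medication free for more than 1 week". For BD, the inclusion list asks for patients "meeting the DSM-5 criteria for major depressive episode of bipolar I disorder or bipolar II disorder" together with age, severity and ability to be interviewed. The BD exclusion list bars patients who "had electroconvulsive therapy, modified electroconvulsive therapy, or repetitive transcranial magnetic stimulation in the past 6 months". Neither BD list mentions drugs.

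Statistical methods for primary and secondary outcomes {20a} does name covariates (gender, age, education, baseline severity), but for the HAMD model of the randomised comparison. The Limitation section concedes that the one-week washout is short, but relates this only to the intervention effects.

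**The concern.** Adjustment is specified for the comparison that randomisation already protects, and not for the one between groups formed by diagnosis. The imbalance does not depend on chance, because the eligibility rules permit it: at blood sampling and scanning a BD patient may be taking drugs, while an AFD patient at baseline may not.

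A drug that shifts a metabolite, a cognitive score or an MRI measure then produces a BD mean that differs from the AFD mean without any difference between the disorders. The named tests, applied as stated, cannot tell the two apart, and a larger sample only makes the spurious difference easier to detect. The dissemination plan aims at clinical guidelines and textbooks, so a BD drug signature could be carried forward as a marker that distinguishes AFD from BD.

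**Working it through.** **The plan's own figure.** The only sample-size calculation, in Sample size {14}, concerns the randomised arms. It reproduces: n = 2 × (1.960 + 0.842)² / 0.5² = 62.8, so 63 per group, and 63 / 0.70 = 90. It says nothing about the biomarker comparison, for which no figure is given.

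**Inputs from the documents.** AFD 480 and BD 100 (Recruitment {15}). A two-sided 5% level is assumed for each marker; the article states that level only for the trial's sample size.

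**Inputs assumed.** m is the share of BD patients on a drug that affects the marker: 25%, 50% or 100%. s is the shift it causes: 0.2, 0.3 or 0.5 SD. There is no true AFD–BD difference. The documents give neither m nor s.

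**Formulas.**
- Bias in the AFD–BD difference: b = m × s.
- Variance in BD, in SD² units: v = 1 + m(1 − m)s².
- Standard error: SE = √(1/480 + v/100).
- False-positive rate: Φ(b/SE − 1.96) + Φ(−b/SE − 1.96).

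**One case in full** (m = 0.50, s = 0.3): b = 0.15; v = 1 + 0.25 × 0.09 = 1.0225; SE = √(0.00208 + 0.01023) = 0.111; b/SE = 1.352; rate = Φ(−0.608) + Φ(−3.312) = 0.272.

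**False-positive rate per marker, AFD versus BD:**

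| Share of BD medicated | s = 0.2 SD | s = 0.3 SD | s = 0.5 SD |
|---|---|---|---|
| 0% | 5% | 5% | 5% |
| 25% | 7% | 10% | 20% |
| 50% | 15% | 27% | 60% |
| 100% | 44% | 78% | 99.5% |

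**Omnibus test over the four groups.** If only the BD mean is shifted by b, the noncentrality is b² × 100 × 580/680, however the 480 AFD patients split into first-episode and recurrent. With 3 and 676 degrees of freedom, and taking the variance as 1 throughout, b = 0.10 gives 0.85 and a rejection rate of 0.105; b = 0.25 gives 5.33 and 0.464. These are the 0.2 and 0.5 SD cases with half of BD medicated. The omnibus test is less sensitive than the pairwise contrast but still well above 5%.

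**AFD versus healthy controls.** Current BD medication does not enter this contrast. Drug effects reach it only if they outlast the washout in AFD patients who were previously treated.

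**The case against.** The strongest reply is that this is a condensed article. The full protocol exists separately and an analysis plan is mentioned, so much may be settled there. The study is labelled exploratory, and the abstract mentions multivariate informatics analyses for recognising AFD, so the named tests are not the only analysis of this aim. The word unadjusted does not appear; it is inferred from the tests named and from the contrast with the HAMD model. ANOVA can carry further factors.

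Part of this stands, and it limits the point. A reader might infer three stronger claims that the documents do not support.

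- **Scanner effects will pass as AFD markers.** The article says "Neuroimaging data are acquired using the 3.0-T scanner at available clinical sites", with five recruiting sites. Bias needs the groups to be spread unequally over scanners, and nothing says they are. With an assumed 0.5 SD shift at one site and √(1/480 + 1/100) = 0.110 as standard error, the false-positive rate is 5% if the groups' shares at that site are equal, and 7%, 15% or 44% if they differ by 10, 20 or 40 percentage points. Harmonisation may be described elsewhere.
- **Groups are unmatched and false discoveries uncontrolled.** The article is silent on both, and such detail is commonly left to an analysis plan. Silence here is no finding.
- **Most AFD–BD markers would be false.** That requires a high medicated share and a sizeable drug effect, neither of which is documented.

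What the reply does not remove is the medication asymmetry. Both halves of it are in the text: the eligibility rules create it, and the comparison names tests that do not deal with it. The abstract describes no control for medication either.

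**Conclusion.** The concern holds for the AFD–BD contrast and for the omnibus test. Followed as written, the plan can report an effect of BD medication as a biomarker difference. It does not follow that it will, because the medicated share is unknown.

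Across the assumed range the false-positive rate per marker runs from about 7% to over 99%, against a nominal 5%. It stays close to nominal only if few BD patients are medicated and drug effects are small. The figures assume all 480 and 100 patients contribute; MRI numbers may be smaller, which would lower the rates but not the bias. AFD versus healthy controls is affected only through residual effects after washout.

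The point should be acted on because it touches the declared primary aim and a better method is at hand. It leaves the randomised treatment comparison untouched.

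**What to change.** In Methods for additional analyses {20b}:

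1. Replace the named tests with linear or logistic models for group, adjusted for age, sex, education and site (scanner for MRI measures).
2. Tabulate medication at blood sampling and at scanning, by group.
3. Prespecify two sensitivity analyses, reported as estimates with confidence intervals: AFD versus BD in medication-free BD patients, and AFD versus healthy controls in drug-naive AFD patients.
4. Do not rely on a medication covariate alone. AFD patients are unmedicated at baseline by design, so among patients current medication varies only within BD. If nearly all BD patients are medicated, drug and diagnosis cannot be separated by adjustment.
5. Describe an AFD–BD marker that is not supported in medication-free patients as possibly due to medication. Do not discard it on significance alone, since that subset may be small.

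The cost is wording and modest extra analysis. Plans for assessment and collection of outcomes {18a} already records earlier medication and the current prescription; the sponsor should confirm that this captures BD patients' status at sampling and scanning. The price is fewer markers claimed, and a wide interval for AFD versus BD if few BD patients are medication-free.

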### Data collection and management

#### Plans for assessment and collection of outcomes {18a}

M.I.N.I International Neuropsychiatric Interview (MINI) [19] is used to conduct a comprehensive screening. HAMD-24 and Quick Inventory of Depressive Symptomatology (self-report) with 16 items (QIDS-SR16) [20] are applied to evaluate depressive symptoms, Hamilton’s Anxiety Scale (HAMA) [21] is used to assess anxious symptoms, HCL-32 is performed to recognize mania or hypomania symptoms, and Quality of Life Scale with 6 items (QOL-6) [22] is used to evaluate the life quality briefly. Additionally, family history, physical or mental comorbidity, the medication used before, prescription for this time, number of episodes, first-onset time and age, and duration of illness are also questioned and recorded. Adverse events are recorded in adverse events report (AER) forms when needed during the follow-up period. Cognitive function is assessed using the MATRICS Consensus Cognitive Battery (MCCB) [23]. MCCB consists of 10 subtests that mainly reflect the cognitive function of 7 cognitive domains including speed of processing, attention and vigilance, working memory, verbal learning, visual learning, reasoning and problem-solving, and social cognition.

After the 12-week randomized intervention, patients with AFD will be followed up until switching to BD for a maximum of 4 years. Face-to-face interviews, including clinical and neurocognitive assessments, MRI scans, and blood specimen collection, will be scheduled for 12 weeks, 1 year, and 4 years. The interim interviews of clinical assessments will be performed at 2 weeks, 4 weeks, 8 weeks, 6 months, 2 years, and 3 years through offline or online approaches. Patients with AFD will undergo a semi-structured interview at the follow-up time points to determine whether they have experienced mania or hypomania or have been diagnosed with bipolar disorder by psychiatrists during the interval since the previous follow-up. If a patient has experienced mania or hypomania or has been diagnosed with bipolar disorder by psychiatrists during the interval, multidimensional data will be recollected and follow-up will be terminated.

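### The bipolar-conversion model uses a yes/no outcome and changes over the whole follow-up, with no cut-off before the switch and no handling of unequal follow-up

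*Protocol article*

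**What the plan says.** The third aim in the article's Objectives section is to "build a clinical early warning model to predict the conversion of AFD to BD". The section on additional analyses {20b} describes the model in three parts.

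- **Predictors and outcome:** "Multidimensional data obtained at baseline and their changes during the follow-up period will be used to predict the binary outcome", the outcome being a switch to mania or hypomania or none.
- **Performance:** "The concordance index will be calculated to assess the discrimination of the model".
- **Construction:** left to biomedical engineering collaborators.

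The section on outcome assessment {18a} sets the follow-up.

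- **Length:** "patients with AFD will be followed up until switching to BD for a maximum of 4 years".
- **Ascertainment:** a semi-structured interview at each follow-up point asks whether the patient has had mania or hypomania, or has been "diagnosed with bipolar disorder by psychiatrists during the interval since the previous follow-up".
- **At a switch:** "multidimensional data will be recollected and follow-up will be terminated".
- **Visits:** full assessments (clinical, cognitive, MRI, blood) are at 12 weeks, 1 year and 4 years. Clinical-only visits are at 2, 4 and 8 weeks, 6 months, 2 years and 3 years.

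The section on missing data {20c} plans multiple imputation, with complete-case and replaced-value sensitivity analyses. It does not mention the conversion outcome.

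**The concern.** An early-warning model may use only what is known before the event. Here the predictors include changes over a follow-up period that, for a converter, ends at the visit where the switch is found. That visit comes after the event, because the interview looks back over the preceding interval. Data from it could reflect the episode or its aftermath instead of predicting it. The period over which change is measured also depends on the outcome: it stops early in converters and can run to 4 years in the others.

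The yes/no outcome raises a second problem. It has no place for a patient last seen unconverted at, say, 6 months, whose 4-year status is unknown. The C-index does not resolve this, because for a binary outcome it equals the area under the ROC curve and makes no use of follow-up time.

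At stake is whether the reported discrimination could be reproduced when a clinician needs the prediction, and whether the predicted risks refer to a defined period.

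**Working it through.** **Stated figures.** The article gives no conversion rate, 4-year loss or target C-index for this model. Its only sample-size calculation concerns the 12-week trial. That reproduces: 2 × (1.960 + 0.842)² / 0.5² = 62.8, so 63 per group, and 63 / 0.70 = 90. It has no bearing here.

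**When the full data exist.** Setting the visit schedule beside the rule for switches:

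| Switch found | Full post-baseline data before the detecting visit | Full data at the detecting visit |
|---|---|---|
| before week 12 | none | recollection |
| at 6 months | week 12 | recollection |
| at 2 or 3 years | week 12, year 1 | recollection |
| at 12 weeks, 1 year or 4 years | earlier full visits, if any | scheduled or recollected |

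For a switch found before week 12, the recollected set is the only source of any MRI, blood or cognitive change. For one found at 2 or 3 years, it is the only full set after year 1. A change over follow-up would naturally draw on it, and nothing in {20b} excludes it.

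**Illustration 1: data from the switch visit enter the change scores.** Assume a marker with no prognostic value. Its change score is N(0, 1) in non-converters and N(s, 1) in converters, where s is the shift at the switch visit in SD units. Then C = Φ(s/√2).

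| s (assumed) | C |
|---|---|
| 0 | 0.50 |
| 0.5 | Φ(0.354) = 0.638 |
| 1.0 | Φ(0.707) = 0.760 |
| 1.5 | Φ(1.061) = 0.856 |

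**Illustration 2: drop-outs forced into a yes/no outcome.** Assume constant, independent hazards over 4 years: λ = −ln(1 − c)/4 for true conversion c, and μ = −ln(1 − d)/4 for 4-year drop-out d.

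- Observed converters: λ/(λ + μ) × (1 − e^(−4(λ + μ))).
- Lost unconverted: μ/(λ + μ) × (1 − e^(−4(λ + μ))).

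Take c = 10% and d = 30%. Then λ = 0.02634, μ = 0.08917, and 1 − e^(−0.462) = 0.370. Observed converters are 0.228 × 0.370 = 8.4%, and 0.772 × 0.370 = 28.6% are lost unconverted. Of 480 patients, about 137 leave without an observed event and about 7.5 of 48 conversions go unseen.

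- **Lost patients scored as not switched:** risk is 8.4% instead of 10%. Across c = 5%, 10% and 20%, the relative understatement is about 5% for d = 10%, 15 to 16% for d = 30%, and 27 to 28% for d = 50%.
- **Heavier loss:** with 15% annual loss and c = 20%, 43.4% are lost unconverted and 14.9% are observed to convert.
- **Lost patients dropped instead (complete cases):** early converters stay in and lost non-converters leave. With c = 10% and d = 30%, risk is 8.44 / (100 − 28.56) = 11.8%, too high.

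The direction of the error thus depends on a rule that the article does not give. Censoring at the last assessment avoids both errors if loss is independent of conversion.

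**The case against.** The strongest reply is that the article permits these errors but does not plan them.

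- **Recollected data.** A reader might infer that they are meant to enter the change scores. No sentence says so; they might serve only to describe the switch. Week-12 and 1-year data supply pre-switch changes for many patients. This stands: the plan lacks a cut-off, but leakage is not stated.
- **Drop-outs.** A reader might infer that they count as non-converters. The article does not say this, and its general plan for multiple imputation points the other way. This stands too, so the understated risk is conditional. But imputation is not tied to the conversion outcome, and the complete-case sensitivity analysis brings its own bias.
- **Manic state.** A reader might infer that the model would simply learn it. With visits up to a year apart, the episode may be over when data are recollected. The shift could be small, and at zero shift C stays at 0.50.
- **Randomised arm, optimism correction and calibration.** The article lists no individual predictors and records prescriptions. Silence on these matters is what a condensed article leaves to the full plan, and is no fault here.
- **Exploratory status.** The model is the third aim, under additional analyses. That lowers the severity.

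What the reply does not remove is the stated method: a binary outcome under variable follow-up, with changes over that follow-up as predictors. An analysis plan that is not shown might define a window, but it would have to narrow the published wording to do so.

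**Conclusion.** The concern holds in this form: the stated method does not confine predictors to the time before the switch, lets change windows differ by outcome, and uses an outcome that cannot represent incomplete follow-up. This conflicts with the early-warning purpose.

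The possible size is material but rests on assumptions. An uninformative marker would show C of about 0.64 to 0.76 if switch-visit data entered the change scores and shifted by 0.5 to 1.0 SD. Conversion risk would be understated by about 5% to 28% in relative terms for 10% to 50% drop-out over 4 years, but only if drop-outs were scored as not switched. The documents supply none of these inputs.

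Severity: should fix. The aim is exploratory and ranked third, and the randomised comparison is unaffected.

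**What to change.** Replace the binary outcome in {20b} with time to conversion, in a discrete-time or interval-censored model because visits are up to a year apart. Censor unconverted patients at their last assessment. Then:

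1. Fit a model on baseline predictors only.
2. Fit a week-12 landmark model on baseline values plus change to week 12, in patients unconverted at week 12, predicting later conversion.
3. Exclude from the predictors every measurement taken at or after the visit that detects the switch. Recollected data may still be used to describe the switch.
4. Report a C-index suited to censored data.

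This needs no new data, only a change of wording and modest extra analysis. The costs are a lower apparent C-index and that changes after week 12 enter only through later landmarks, such as year 1, with fewer patients still at risk.

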### Methods in analysis to handle protocol non-adherence and any statistical methods to handle missing data {20c}

The missing data will be managed using multiple imputation techniques. Sensitivity analysis will be further conducted using data from complete cases and data with replacing values.

### Plans to give access to the full protocol, participant-level data, and statistical code {31c}

The datasets analyzed during the current study and statistical code are available from the corresponding author upon reasonable request, as is the full protocol.

### Oversight and monitoring

#### Composition of the coordinating center and trial steering committee {5d}

The coordinating center is in charge of monitoring, data management, and statistical analysis. SMHC is responsible for designing the trial and making the analysis plan.

